### Design

This study uses a pragmatic stepped-wedge design [44] to evaluate both the effectiveness and implementation strategy of the WIFI program. The CONSORT checklist is presented in Multimedia Appendix 1, and the SPIRIT checklist is presented in Multimedia Appendix 2. We will conduct a multicenter prospective controlled trial, using a stepped-wedge design, comparing the WIFI program integrated into the Reward Policy (intervention group) and the Reward Policy alone (control group) in family caregiving among people living with schizophrenia.

In a SWCRT, all clusters are randomly and sequentially crossed over from control to intervention over a number of time periods [48]. All clusters serve as a control group at the beginning of the study and end up in the intervention group at the end of the study. Compared with traditional randomized controlled trials and parallel cluster studies, a SWCRT enjoys unique ethical benefits since all clusters will ultimately receive the assumingly beneficial intervention at the end of the study [49]. In addition, a SWCRT enables analyses of any temporal effects of the intervention since each cluster acts as its own control and also allows for estimation of both between- and within-cluster effects of the intervention owing to repeated measurements [49]. As a result, a SWCRT design achieves greater statistical power with smaller sample sizes and is more cost-effective than parallel group designs.

In the proposed study, a WIFI program will be implemented sequentially across an 8-month intervention period in the 12 communities by Changsha Psychiatric Hospital. A total of 20 families will be recruited from each community, leading to a total sample of 240 families. Allocation will be determined by an external statistician using a computer-generated random number sequence. Each number will be secretly and securely stored in a sealed envelope by the external statistician until the intervention starts. The first author (YY) will generate the allocation sequence, the medical team will work on enrolling participants, and the second author ([name]) will assign participants to interventions. The 12 communities will be randomized into four groups according to geographic distance and number of people living with schizophrenia to reduce the risk of contamination and group size inequality. After allocation, each group will be randomized to one of four fixed sequences every 2 months during an 8-month intervention period (Table 1 and Figure 2). All communities will receive the usual financial benefit of the Reward Policy as the control condition before the intervention, and then, successively and in random order, will cross over to the WIFI program at 2-month intervals until the study ends.

**Figure 2 figure2:**
[figure not shown]
Flowchart for participant recruitment and allocation. C: community; F: family.

**Table 1 table1:** Design of the four-stage stepped-wedge cluster randomized trial.

Cluster community (CM) group^a^	Assessment^b^				
	Baseline (M_1-2_)^c^	Step 1 (M_3-4_)	Step 2 (M_5-6_)	Step 3 (M_7-8_)	Step 4 (M_9-10_)
CM_1-3_	C^d^	WIFI^e^	WIFI	WIFI	WIFI
CM_4-6_	C	C	WIFI	WIFI	WIFI
CM_7-9_	C	C	C	WIFI	WIFI
CM_10-12_	C	C	C	C	WIFI

^a^Number of clusters=12; number of groups=4; number of clusters per group=3.

^b^Step length=2 months; number of participants per step=20.

^c^M: month.

^d^C: control (Reward Policy alone).

^e^WIFI: WeChat-based Integrative Family Intervention.

### Participants and Recruitment

Recruitment is estimated to start in September 2020. The study aims at recruiting 240 families of people living with schizophrenia from 12 communities affiliated to Changsha Psychiatric Hospital through the “686 Program.” Within each community, 20 eligible people living with schizophrenia will be randomly selected from the registry name list by a statistician, leading to a sampling frame of 240 families of people living with schizophrenia. Each family will be approached and invited to participate in the study during the monthly medicine delivery by the medical team from Changsha Psychiatric Hospital. We do not require both a person living with schizophrenia and a family caregiver to be recruited into the study at the same time. The entire family may benefit from the intervention as long as there is one member from the family participating*.* The medical team has been providing mental health services, including free antipsychotic medicine delivery, in the communities for a long time and thus knows very well about each family having a person living with schizophrenia, which greatly facilitates participant recruitment and retention. Detailed information about the research will be provided both orally and in written format to interested families by the medical team. All families will be fully informed of the study risks and benefits, and their right to drop out of the study at any time (Multimedia Appendix 3). Families agreeing to participate in the study will be invited to scan a WeChat barcode of the research program, so that they can be allocated to receive the intervention in the future. Our research team will include three psychiatrists who will complete clinical assessments of symptoms and functioning of the people living with schizophrenia through WeChat video chat. In addition, 10 postgraduate students will assist people living with schizophrenia and their caregivers to complete online questionnaires through WeChat. The research team will receive extensive training for both the intervention and evaluation to ensure quality and consistency.

Participants of the study will include both people living with schizophrenia and their family members. The inclusion criteria for participating people living with schizophrenia are as follows: (1) registration in the “686 Program;” 2) fulfilling the Chinese Classification of Mental Disorders-3 (CCMD-3) or the International Classification of Diseases-10 (ICD-10) criteria for schizophrenia; (3) age 18 years or older; (4) living with at least one family member; and (5) ability to use a smartphone and WeChat to read and communicate. The inclusion criteria for participating family members are as follows: (1) registration in the Reward Policy and receiving a subsidy for family care; (2) living with a person having schizophrenia for at least the past 2 years; (3) age 18 years or older; 4) involvement with caregiving activities of people living with schizophrenia; (5) ability to use a smartphone and WeChat to read and communicate; and (6) at least one family member having a smartphone with the WeChat app installed.

### Blinding

People living with schizophrenia, family caregivers, medical team members, and researchers cannot be blinded to the allocated treatment. The program team conducting the intervention will not be involved in assessing any of the outcomes. The data analyses by researchers will be blinded.

### Intervention

Participants in the control group will receive the usual financial benefits of the Reward Policy and receive payments from Changsha Psychiatric Hospital. However, they will not have access to the WIFI program since they cannot scan the WeChat barcode for the research.

Participants in the intervention group will receive the usual financial benefits of the Reward Policy as well as the WIFI program that will include the following three key components: psychoeducation through WOA publications, peer-support through a WeChat chat group, and professional support through WeChat private chat and video calls (Table 2).

**Table 2 table2:** Content of the WeChat-based integrative family intervention program.

Component	Format	Frequency	Leader	Possible content/topics
Psychoeducation	WeChat official account publications	Weekly	Psychiatrists and researchers	What is schizophrenia? What causes schizophrenia? How is schizophrenia treated? What can be done to promote recovery in schizophrenia? What are the early signs of relapse? What support do families need? How can feelings of stigma be addressed?
Peer support	WeChat chat group of people living with schizophrenia	Daily	People living with schizophrenia volunteers	Introduce self and tell your story; identify a specific problem encountered to discuss with the group; discuss skills and techniques used to cope with challenging situations; share feelings and resources; organize offline activities for support and stress reduction, such as hiking, dinner, and group meetings.
Peer support	WeChat chat group of caregivers	Daily	Caregiver volunteers	Introduce self and tell your story; identify a specific problem encountered to discuss with the group; discuss skills and techniques used to cope with challenging situations; share feelings and resources; organize offline activities for support and stress reduction, such as hiking, dinner, and group meetings.
Professional support	Private WeChat chat and video call	Monthly	Psychiatrists	Evaluate symptoms and function in people living with schizophrenia; update on medication and treatment; troubleshoot specific problems; provide consultation, guidance, assistance, etc.

### Contamination

Since randomization is performed at the community level, using the stepped-wedge design, the risk of contamination between the control and intervention groups is very low. Moreover, since the intervention is delivered through WeChat and each participant scans the special WeChat barcode of the research program to obtain access to the WIFI program, it is unlikely that participants in the control group will receive the intervention during the control stage. Even if participants in the control group learn about the WeChat account of the research program, they will not be able to add it because the research team will recognize each participant and decline any request from the control group until receiving the allotted sequence to join the intervention. Thus, intervention contamination will be avoided.

### Outcomes

#### Effect Measures

The effect of the intervention will be assessed at the individual level for both family caregivers and people living with schizophrenia.

For family caregivers, the outcomes will include knowledge and skills about caregiving (Knowledge and Skill of Caregiving for Schizophrenia, self-developed), social support (Multidimensional Scale of Perceived Social Support) [50], coping (Simplified Coping Style Questionnaire) [51], perceived stigma (Perceived Devaluation and Discrimination Scale) [52], caregiver burden (Zarit Burden Interview [ZBI]) [53], family functioning (Family Adaptation, Partnership, Growth, Affection and Resolve Index scale) [54,55], positive feelings (Caregiving Rewarding Feelings) [56], perceived stress (Perceived Stress Scale) [57], depression (Patient Health Questionnaire-9 [PHQ-9]) [58], and anxiety (Generalized Anxiety Disorder Scale-7 [GAD-7]) [59].

For people living with schizophrenia, the outcomes will include clinical symptoms (Brief Psychiatric Rating Scale [BPRS]) [60] and overall functioning (Global Assessment of Functioning [GAF]) [61], which will both be rated by psychiatrists. Other outcomes will include self-reported quality of life (World Health Organization Quality of Life Brief Scale) [62], recovery (Recovery Assessment Scale [RAS]) [63], rehospitalization, depression (PHQ-9) [58], and anxiety (GAD-7) [59].

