### Power Analyses

To illustrate the power for analyses of both caregivers and people living with schizophrenia, we can use a baseline ZBI score of 45 for caregivers and a baseline GAF score of 42 for people living with schizophrenia based on previous studies as well as a baseline study conducted by the research team with caregivers and people living with schizophrenia in Hunan province. For a SWCRT with 12 communities over five time periods or steps (baseline and four intervention steps), assuming an intracluster correlation of 0.05, 90% power at a 5% significance level, and 20% dropout ratio, a sample size of 235 is needed to detect a clinically important decrease in caregiver burden as assessed by a decrease in the ZBI score from a baseline of 45 to 30 [50]. Similarly, for people living with schizophrenia, a sample size of 210 is needed to observe an increase in the GAF score from a baseline of 42 to 52, assuming α=.05, β=.15, and 20% attrition. Based on the above calculations, we decided on a sample size of 20 families per community (240 families in total), which will be sufficient to detect expected improvements in both caregiver burden and functioning of people living with schizophrenia.

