## Discussion

Using a SWCRT design, the proposed study will develop a WIFI program fully aligned with the Reward Policy and test its effectiveness. Expected results will include the following: (1) significant improvement in outcomes for both people living with schizophrenia and their family members owing to WIFI program participation; (2) stronger impact for WIFI combined with the Reward Policy than the Reward Policy alone; and (3) development of a cost-effective replicable family management model for schizophrenia that can be integrated into the current national Reward Policy.

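### No primary outcome is named among 17 effect outcomes, although the sample size rests only on ZBI and GAF

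*Protocol article*

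**What the plan says.** - **Outcomes (Methods, Effect Measures).** The caregiver list begins "For family caregivers, the outcomes will include knowledge and skills about caregiving" and has 10 entries: knowledge and skills, social support, coping, stigma, ZBI, family functioning, positive feelings, perceived stress, PHQ-9 and GAD-7. The patient list has 7: BPRS and GAF, both rated by psychiatrists, followed by a sentence that begins "Other outcomes will include self-reported quality of life" and adds recovery, rehospitalization, PHQ-9 and GAD-7. Table 3 repeats the same 17, each at all five assessments. Nowhere is an effect outcome called primary or secondary.
- **Sample size (Methods, Power Analyses).** ZBI and GAF are brought in as illustrations of power. For ZBI the text reads "assuming an intracluster correlation of 0.05, 90% power at a 5% significance level, and 20% dropout ratio, a sample size of 235 is needed"; the target is "a decrease in the ZBI score from a baseline of 45 to 30". For GAF, 210 are needed for a rise from 42 to 52, "assuming α=.05, β=.15, and 20% attrition". The planned total is 240 families, 20 in each of 12 communities.
- **Analysis (Methods, Statistical Analysis).** One mixed-model approach serves all outcomes. No test level, sidedness or order of testing is given.
- **Expected result (Discussion).** "significant improvement in outcomes for both people living with schizophrenia and their family members owing to WIFI program participation". No outcome is singled out.

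**The concern.** The primary outcome defines the question and the sample size, so it belongs in the protocol. A multiplicity procedure may wait for the analysis plan; the choice of what is primary should not. The two outcomes that justify 240 families have no stated priority when the effect is judged, and a success could be reported on any of the 15 that were never sized.

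Two features of the trial make this matter more. Participants, medical team and researchers are unblinded (Blinding), and most of the outcomes are self-reported. The article also undertakes to report changes to outcomes (Ethical Consideration), but a shift of emphasis among 17 unranked outcomes would leave nothing to report.

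**Working it through.** **1. Inputs.** From the article: 10 + 7 = 17 outcomes; 5% level (power section only); ICC 0.05 (stated for ZBI; assumed to carry over to GAF); power 90% at N = 235 (ZBI) and 85% at N = 210 (GAF); 20% dropout; 12 communities, five periods, four sequences; 240 families. Assumed, because the article does not give them: two-sided tests, all 17 tested at 5%, and the correlation between test statistics (a common value from 0 to 0.7).

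**2. The stated sample sizes.** No SD is given for either scale, so 235 and 210 can be neither reproduced nor refuted. Solving backwards with the Hussey-Hughes variance gives SDs of about 42 (ZBI) and 29 (GAF) if N is measured in every period, or about 21 and 14 if N is the total number of observations.

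**3. False results if all 17 are tested and none has a true effect.**

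Independent tests:
- either direction: 1 - 0.95^17 = 0.582
- improvement only: 1 - 0.975^17 = 0.350
- expected number of false rejections: 17 x 0.05 = 0.85

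Correlated tests (equicorrelated normal statistics, 400,000 draws):

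| Common correlation | Any false result, either direction | False improvement |
|---|---|---|
| 0 | 58% | 35% |
| 0.3 | 49% | 25% |
| 0.5 | 39% | 19% |
| 0.7 | 27% | 14% |

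**4. If at least one result is needed in each population.**
- Either direction, independent: (1 - 0.95^10)(1 - 0.95^7) = 0.401 x 0.302 = 0.121
- Improvement only, independent: (1 - 0.975^10)(1 - 0.975^7) = 0.224 x 0.162 = 0.036
- At correlations 0.3, 0.5 and 0.7: about 13%, 13% and 12% in either direction; about 6.2%, 6.5% and 6.0% for improvement only.

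The ranges are therefore about 12-13% and about 4-7%.

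**5. Only ZBI and GAF, each at 5%, independent.** 1 - 0.95^2 = 0.0975. Two primary outcomes still need a rule.

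**6. Power if alpha were split to 2.5% each.** At the stated N the figures would be Phi(1.960 + 1.282 - 2.241) = 84% for ZBI (N = 235) and Phi(1.960 + 1.036 - 2.241) = 77% for GAF (N = 210). The trial plans 240, so the effect-to-standard-error ratio must be rescaled. No SD is needed, because only the ratio of variances enters.

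In units of the total variance, with m completers per community and period, tau2 = 0.05 and s2 = 0.95/m, the Hussey-Hughes variance for this layout is 12 s2 (s2 + 5 tau2) / (90 s2 + 270 tau2).
- 240 families: m = 0.8 x 240/12 = 16, variance 0.01170
- 235: m = 15.67, variance 0.01192
- 210: m = 14, variance 0.01320

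Rescaled:
- ZBI: 3.242 x sqrt(0.01192/0.01170) = 3.273. Power is Phi(3.273 - 1.960) = 91% at 5% and Phi(3.273 - 2.241) = 85% at 2.5%.
- GAF: 2.996 x sqrt(0.01320/0.01170) = 3.183. Power is Phi(3.183 - 1.960) = 89% at 5% and Phi(3.183 - 2.241) = 83% at 2.5%.

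Taking N as total observations (m = N x 0.8/60) gives the same rounded figures.

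**The case against.** The best defence is that the outcomes are not wholly undifferentiated. BPRS and GAF come first in the patient list and the rest follow as other outcomes; ZBI and GAF carry the sample size; ZBI, BPRS and GAF are the examples in the cost-effectiveness section. A journal article may also leave multiplicity to an analysis plan.

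Much of this is fair, but it does not supply a primary outcome. The patient list separates psychiatrist-rated measures from the remaining ones without ranking them. The caregiver list has no such split. The cost-effectiveness examples are a different set from the sized pair.

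The objection does stand against several stronger readings that a reader might infer:
- **That the plan tests each of the 17 at 5%.** The article does not say so; 5% appears only in the power section.
- **That any one significant result would establish effectiveness.** No such rule is stated. The Discussion sentence is an expectation, not a decision rule, and it speaks of both populations, which is why step 4 of the working is relevant.
- **That 27-58% is the chance of a false improvement.** Those figures count false results in either direction. For improvement the range is about 14-35%. A figure of 58% for improvement would need independent one-sided 5% tests, and sidedness is not stated.
- **That the lower ends come from the trial.** They rest on an assumed correlation of 0.7. The upper ends assume independence, which is unlikely for related scales.

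Whether two populations that were sized separately should share one 5% is also a design choice that the article does not settle.

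**Conclusion.** The concern holds in a limited form. The article lists 17 effect outcomes, names none as primary, sizes only ZBI and GAF, and words its expected result so that it does not say which outcomes count. That is a protocol matter and leaves the effectiveness claim open to selection.

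The size depends on assumptions about testing that the article does not state. With two-sided 5% tests of all 17 and no true effects, at least one false significant result has a chance of up to 58%, and a false improvement up to 35%; at an assumed correlation of 0.7 these fall to about 27% and 14%. Read as requiring a result in both populations, the figures are about 12-13% and 4-7%. Even the lowest of these exceeds the 2.5% that a single two-sided test carries for a false improvement. The article supports neither a rule that any single result suffices nor a stated 5% test of every outcome.

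**What to change.** 1. In Effect Measures, name ZBI (caregivers) and GAF (people living with schizophrenia) as the primary outcomes, because these are the two that were sized.
2. State how the error is controlled across them. One option is the fixed order ZBI then GAF, each at 5%, which keeps the stated 90% power for ZBI. Another is Holm.
3. Label the other 15 outcomes secondary, with no confirmatory claim.
4. Reword the first expected result in the Discussion to refer to ZBI and GAF.
5. If alpha is split instead, recompute the power at the planned 240 families: about 85% for ZBI and 83% for GAF under the stated assumptions. Do not write 84% and 77%, which belong to 235 and 210.

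The cost is wording only, with no extra families. Under the fixed order, GAF is confirmatory only if ZBI succeeds. An alpha split costs about 6 points of power on each outcome at 240 families (91% to 85% and 89% to 83%).

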#### Potential Confounding Factors

At baseline, we will also collect information about potential confounding factors by adjusting for the following: (1) sociodemographic data, such as age, gender, education, and occupation; (2) clinical data, such as diagnosis type of schizophrenia, length of illness, and length of caregiving; and (3) WeChat use intensity as assessed by the WeChat Use Intensity Questionnaire [64,65].

#### Cost Measures

Costs will be measured from a societal perspective and consist of at least the following three levels: (1) costs of the intervention, (2) health care utilization costs, and (3) costs associated with lost productivity. All of the costs will be converted to that for the year 2019 using consumer price indices.

The intervention costs pertain to implementation and operation of the WIFI program. A bottom-up approach will be used to assess the intervention costs, which may include but are not limited to (1) training of psychiatrists, researchers, and other project team members and (2) the WeChat intervention (WOA fee, administrator time, consultation fee of the psychiatrists, etc).

The health care utilization costs pertain to medical care for both people living with schizophrenia and family caregivers. A monthly cost diary will be used to retrospectively track medical expenses incurred by people living with schizophrenia and family caregivers, which may include but are not limited to (1) visits to health care professionals in primary or secondary care; (2) hospitalization; (3) visits to alternative medicine therapists; (4) medication; and (5) other nonmedical expenses associated with medical care, such as transportation, food, and lodging. Health care utilization costs will be estimated by China guideline prices that are supplemented by population-based estimates in the literature.

The costs associated with productivity loss will be assessed at both the people living with schizophrenia and caregiver levels. For both people living with schizophrenia and caregivers, costs include absenteeism due to sick leave, which will be assessed by monthly sick leave calendars. The human capital approach will be used to calculate the costs of losses to production due to sickness or caregiving (net number of days on leave during follow-up multiplied by the daily wage of the worker if employed or an equivalent value if unemployed).

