**Figure 1 figure1:**
[figure not shown]
Theoretical framework of the proposed study. PLS: people living with schizophrenia.

Consistent with the literature, three components are included in the WIFI program to provide education and support to families (psychoeducation, peer support, and professional support) (Figure 1). WeChat will provide access for caregivers and people living with schizophrenia to each of these intervention components. Psychoeducation and support will increase knowledge and skills, as well as social support (peer and professional) and coping to reduce perceived stigma and caregiver burden. In addition, these components are expected to enhance family functioning and positive feelings, such that emotional distress will be reduced. Finally, these effects are hypothesized to reduce caregiving costs. For people living with schizophrenia, these components are expected to enhance the overall quality of care in the community, which is hypothesized to reduce symptoms in people living with schizophrenia and enhance functioning, increase quality of life and recovery, and decrease rehospitalization, thus reducing overall health care costs.

This paper describes the protocol of a study designed to assess the impact of a WIFI program fully aligned with the Reward Policy for families caring for people living with schizophrenia compared with the Reward Policy alone. The specific aims are as follows: (1) compare the effects of the WIFI program plus the Reward Policy with the Reward Policy alone on caregiving and the health outcomes of family caregivers and people living with schizophrenia, such as knowledge and skills, social support and coping, burden, family functioning, positive feelings, and psychological distress of caregivers, as well as symptoms, functioning, and recovery of people living with schizophrenia; (2) compare the total cost of the WIFI program plus the Reward Policy with the Reward Policy alone, including the program itself, health care utilization of people living with schizophrenia and family caregivers, and production loss of family caregivers; and (3) conduct a process evaluation of the WIFI program to assess fidelity and quality of program implementation, as well as user attitudes toward the program. To simultaneously assess intervention effectiveness and implementation strategies using mixed methods in “real-life” health care settings, we used a stepped-wedge cluster randomized trial (SWCRT) design [44].

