**Cost**						
	WIFI program (bottom-up approach)	Yes	Yes	Yes	Yes	Yes
	Health care utilization (cost dairy)	Yes	Yes	Yes	Yes	Yes
	Productivity loss (sick leave calendar)	Yes	Yes	Yes	Yes	Yes

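### The costing formula needs days lost to caregiving and days lost by unemployed people, but the only measure named is sick leave from a sick leave calendar

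*Protocol article*

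**What the plan says.** Aim 2, at the end of the Theoretical Framework section, lists "production loss of family caregivers" among the components of total cost. Under Cost Measures, "Costs will be measured from a societal perspective", and lost productivity is one of three cost levels. It covers both groups: "The costs associated with productivity loss will be assessed at both the people living with schizophrenia and caregiver levels".

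The measurement sentence reads: "costs include absenteeism due to sick leave, which will be assessed by monthly sick leave calendars". The valuation sentence that follows says the human capital approach will "calculate the costs of losses to production due to sickness or caregiving", with the amount defined as "net number of days on leave during follow-up multiplied by the daily wage of the worker if employed or an equivalent value if unemployed".

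In the cost block of Table 3 the matching row begins "Productivity loss (sick leave calendar", and no second instrument is listed for lost time. The other participant-completed cost instrument, the monthly cost diary, tracks medical expenses and related outlays such as transport, food and lodging. It is not described as recording time.

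**The concern.** The measurement sentence and the valuation sentence do not fit together. The first records sick leave. The second puts a price on time lost to sickness or to caregiving, for people with and without a job. A day that a caregiver takes off to look after a relative is not that caregiver's sick leave, and a person without a job has no sick leave to enter. For these two kinds of loss the plan gives a price but no stated quantity to multiply it by.

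At stake is the economic comparison, not the clinical effect estimates. The Cost-Effectiveness Analyses section puts the difference in mean total costs in the numerator of every incremental ratio. The theoretical framework expects the programme to lower caregiving costs. If caregiving days are not collected, any change in them, in either direction, is absent from that numerator, and no later analysis can restore it.

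**Working it through.** There is no productivity-loss figure in the article to reproduce: no days, wage or employment share. The main check is therefore textual.

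**1. Match each loss in the formula to a stated source.**

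| Loss the formula values | Stated source of days |
|---|---|
| Employed caregiver or patient, own sickness | Sick leave calendar |
| Employed caregiver, time lost to caregiving | None stated |
| Unemployed caregiver or patient, own sickness | None stated; no sick leave exists to record |
| Unemployed caregiver, time lost to caregiving | None stated |

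**2. Look for another instrument.** The cost diary covers expenses, not time. Data Collection and Management presents Table 3 as an overview of all outcome measures and instruments, and the table gives only the calendar for productivity loss. The table is not complete, however. It omits the EQ-5D, which the Cost-Effectiveness Analyses section uses. Table 3 alone therefore does not prove that no other instrument exists, but Cost Measures independently names the same single one.

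**3. Compare who is counted.** Aim 2 lists production loss for caregivers only. Cost Measures counts patients as well.

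**4. Illustrate the size.** Only the exposure time comes from the article. Table 1 gives the four groups 4, 3, 2 and 1 intervention steps of 2 months each:

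- Exposure by group: 8, 6, 4 and 2 months.
- Mean exposure, with three communities per group and 20 families per community: (8 + 6 + 4 + 2) / 4 = 5 months.

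Two inputs are assumed, with no source in the article: 1 to 4 caregiving days lost per month, and a 25% fall under the programme that applies in full from the start of exposure. Then:

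- Change not recorded per family = fall × days per month × months exposed.
- Low end: 0.25 × 1 × 5 = 1.25 days.
- High end: 0.25 × 4 × 5 = 5 days.
- First group only (8 months): 0.25 × 1 × 8 = 2 days to 0.25 × 4 × 8 = 8 days.
- Last group only (2 months): 0.25 × 1 × 2 = 0.5 days to 0.25 × 4 × 2 = 2 days.

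The result scales in proportion to each assumed input. It cannot be turned into money, because the article gives no daily wage or equivalent value.

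**The case against.** The best defence is that the calendar is loosely named. The formula counts days on leave, not days of sick leave, and expressly covers caregiving and unemployed people. The wording is open: costs are said to include sick leave, and to consist of at least three levels. The article condenses a fuller protocol, and the fields of a cost form are commonly left to that protocol or to the form itself. The calendar may already ask for caregiving days.

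Much of this stands. The form is not shown, so nobody can say from the article that caregiving days will in fact go uncollected. What does not stand is that this is only an omitted detail. The article states the instrument in two places and states a formula that the instrument, as described, cannot feed. Even if leave is read broadly enough to include care leave, there is still no day count for someone without a job, whom the formula includes.

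A reader might go further and infer that Aim 2's item has no input at all, or that most caregiver production loss will go unrecorded. The first is wrong, because the calendar applies to caregivers and a caregiver's own sick leave is production loss of a caregiver. The second cannot be derived. The captured share is sick days / (sick days + caregiving days), and the article gives neither quantity. Nor does it support a claim that caregiving time is the cost most likely to change. The theoretical framework also expects less rehospitalization and lower health care costs, and does not rank them.

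**Conclusion.** The point holds as a mismatch between a stated instrument and a stated formula. As written, own sick leave is captured. Days lost to caregiving, and days lost by unemployed caregivers or patients, have no stated source. The caregiving-related part of Aim 2's caregiver production loss could therefore be missing from the societal cost difference and the ratios built on it.

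The size is unknown. The 1.25 to 5 days per family show only what could be missed under the assumed inputs. It would be wrong to apply the first group's 2 to 8 days to every family, since only that group has 8 months of exposure. The conclusion assumes that the calendar records what its name and description say. If the actual form already collects caregiving days and unemployed people's lost days, only the wording needs correcting. This is a modest point about the economic aim, worth settling because the repair is cheap and cannot be made afterwards.

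**What to change.** Before trial data collection starts, specify that the monthly calendar records days lost from paid work or usual activity, in two lines (own sickness and caregiving), and that employed and unemployed respondents both complete it. Use those days as the quantity in the human capital formula. Rename the instrument in Cost Measures and Table 3 to match, since sick leave calendar no longer describes it. Align Aim 2 with Cost Measures on whether patients' lost production is counted.

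The cost is about two extra lines on a form already completed each month, or roughly a minute of respondent time. If the extra burden is not wanted, the alternative is to narrow Aim 2 and the formula to sickness absence and state that caregiving time is not costed. That would be consistent, but it gives up part of the societal perspective.
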